**Figure 3 figure3:**
[figure not shown]
Study outcome assessment timeline. PMSI: Programme de Médicalisation des Systèmes d’Information.

ITS analysis is a quasi-experimental design used to evaluate the longitudinal effect of an intervention by analyzing data collected at multiple time points before and after the intervention is implemented. This method enables the detection of both abrupt changes in outcome level and gradual changes in trend that may result from the intervention. ITS is particularly valuable when randomized controlled trials are not feasible, because it allows causal inference from observational data by controlling for underlying trends and temporal confounders. By modeling the preintervention trajectory and comparing it to the postintervention pattern, ITS helps determine whether observed changes are likely attributable to the intervention rather than to external factors or natural fluctuations over time.

Secondary outcomes—including the incidence of ACS, TIA, peripheral arterial disease, aneurysms, and ESRD, as well as cardiovascular and renal mortality—will also be analyzed using ITS models. ITS will help determine whether these outcomes exhibit a significant change in their rate or trajectory after the intervention. Subanalyses will compare trends in populations residing in intervention and nonintervention neighborhoods within the CACL and between the intervention region and other areas of French Guiana where the intervention was not deployed. Comparisons will further be stratified by socioeconomic status markers (eg, French universal health coverage, *aide médicale de l'état* [AME] eligibility, or absence of coverage) when available in the source databases.

For participant-level data obtained through questionnaires (eg, sociodemographic characteristics, adherence indicators, and antihypertensive treatment uptake), analyses will include paired comparisons for repeated measures, using the McNemar test [34] or the Wilcoxon signed-rank tests [35] depending on the data type and distribution.

McNemar test is a nonparametric method used to analyze paired nominal data, particularly in situations where the same participants are measured at 2 time points, such as before and after an intervention. It is designed to detect changes in proportions by focusing exclusively on discordant pairs—cases where the response changed between the 2 time points—while ignoring concordant pairs in which no change occurred. This makes it especially suitable for evaluating shifts in binary outcomes within matched or repeated-measures designs, where observations are not independent.

Trends in antihypertensive prescription volumes, obtained from health insurance reimbursement data, will also be evaluated over the preintervention and postintervention periods using ITS models to assess the effect of the intervention at the population level.

Missing data will be systematically evaluated for all variables. For descriptive analyses, the number of participants with available data will be reported. For analytical purposes, the mechanism of missingness will be assessed (eg, missing completely at random, missing at random, or missing not at random). If data are found to be missing at random, multiple imputation via chained equations (MICE) [36] will be considered for inclusion in multivariable and ITS analyses. MICE is a flexible and iterative method for handling missing data by creating multiple complete datasets. It works by modeling each variable with missing values conditionally on all other variables in the dataset, using appropriate regression models depending on the type of variable (eg, linear for continuous variables and logistic for binary variables). This chained approach allows the preservation of complex relationships among variables and accommodates different data types, improving the validity and efficiency of statistical inferences drawn from incomplete data.

As a sensitivity check, complete-case analyses will also be performed. The influence of missing data on primary and secondary outcomes will be explicitly reported.

Sample size calculations were conducted using the following two complementary approaches.

The primary approach uses the chi-square test; approximately 350 patients with stroke are admitted annually to the Centre Hospitalier de Cayenne, with 68% (n≈238) occurring among socioeconomically precarious patients. Assuming the intervention leads to a 30% reduction in stroke incidence within this population—consistent with previous international interventions—a postintervention count of approximately 167 strokes per year (a reduction from 238) is anticipated. To detect this effect with 90% power at a 5% significance level (α=.05) using a 2-sided chi-square test comparing proportions before and after the intervention, a minimum of 367 cumulative postintervention stroke cases over a 2-year period is required.

Second, a segmented regression (ITS) analysis will be used to complement the chi-square test by examining both immediate level changes and slope changes after the intervention. On the basis of 60 monthly preintervention observations (5 years) and 24 monthly postintervention observations (2 years), and assuming autocorrelation (ρ=0.3-0.5) typical of health administrative data, this design provides adequate power (>80%) to detect a change in slope corresponding to a 20% to 30% reduction in incidence, assuming a baseline coefficient of variation of 15% to 20% in monthly stroke counts.

The chi-square test provides a straightforward test of the primary hypothesis, while ITS analysis accounts for underlying temporal trends and potential confounders, offering a more nuanced understanding of intervention effects. Both analyses will be reported, with ITS serving as the primary confirmatory analysis and the chi-square test as a sensitivity check.

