### Objectives

#### Primary Objective

The primary objective is to determine whether a community-based hypertension screening and referral intervention delivered by trained health mediators is superior to standard health service delivery in reducing the incidence of stroke (*accidents vasculaires cérébraux* [AVC]) over a 2-year period, compared to the 5-year preintervention period, among adults residing in the CACL region of French Guiana.

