### Statistical Analysis

Statistical analyses will be conducted using Stata (version 19; StataCorp). Continuous variables will be described using means and SDs when normally distributed; for skewed distributions, medians and IQR will be reported. Normality will be assessed using visual inspection of histograms and quantile-quantile plots and confirmed with the Shapiro-Wilk test.

Comparisons of continuous variables between groups (eg, before vs after the intervention and intervention vs control regions) will be performed using the Student *t* test or the Mann-Whitney *U* test, as appropriate. The Student *t* test is a statistical method used to determine whether the means of 2 independent groups are significantly different from each other. It assumes that the data in each group are approximately normally distributed and that the variances are equal or similar.

Categorical variables will be summarized as absolute frequencies and percentages. Between-group comparisons will be conducted using chi-square tests or Fisher exact tests.

All statistical comparisons will be 2-sided, and results will be considered statistically significant if *P*<.05. Corresponding 95% CIs will be reported for all estimated parameters.

The primary outcome analysis will assess the difference in stroke incidence before and after the 2-year intervention period among residents of precarious neighborhoods within the CACL of French Guiana. Stroke incidence, derived from PMSI hospitalization data, will be compared across the 2 periods using the chi-square test. To evaluate temporal trends and detect structural breaks attributable to the intervention, segmented regression of interrupted time series (ITS) [33] data will be applied. The ITS model will estimate the immediate change in level and the change in slope after the intervention, while adjusting for autocorrelation and seasonality as necessary based on model diagnostics (Figure 3).

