## Results

This study was funded in 2022 and registered on ClinicalTrials.gov in April 2023 (NCT05814068). Recruitment for this study began in September 2023 and concluded on September 4, 2025, marking the end of the 24-month intervention period. During this period, 23,289 participants benefited from the intervention (ie, received at least 1 BP measurement and health education session), including 10,901 (46.8%) who completed the full enrollment questionnaire. Three-month telephone follow-up for participants with elevated BP was conducted as scheduled and completed by December 2025. Case report form (CRF) data entry and quality monitoring procedures were in progress as of February 2026, with database lock planned for March 2026 and primary outcome analysis expected between April 2026 and May 2026.

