However, several limitations must be acknowledged. The quasi-experimental design without randomization means that temporal confounders (such as concurrent public health campaigns, changes in health care access, or secular trends in treatment patterns) may influence outcomes independently of the intervention. Although we will attempt to control for these through comparison with nonintervention regions in French Guiana, unmeasured confounding remains possible. Reliance on administrative datasets, while ensuring comprehensive capture, may be subject to coding inaccuracies or changes in diagnostic practices over time. However, the use of validated *International Statistical Classification of Diseases and Related Health Problems, 10th revision* (ICD-10) codes for stroke diagnosis and the consistency of PMSI reporting requirements over the study period minimize this concern. Implementation heterogeneity across neighborhoods (varying in size, accessibility, and population composition) may introduce variability in intervention dose and reach. We will document coverage rates by neighborhood and explore heterogeneity in subgroup analyses, but differences in how intensively the intervention was implemented across neighborhoods may influence the results. For secondary outcomes assessed through participant questionnaires and telephone follow-up (eg, referral adherence, treatment initiation, and satisfaction), self-reported data may be subject to social desirability and recall biases. Additionally, loss to follow-up during the 3-month telephone interviews may affect internal validity for these secondary end points, although we plan to use multiple imputation techniques and will report sensitivity analyses restricted to complete cases. These limitations, however, do not affect the primary outcome analysis, which relies exclusively on objective administrative data. Finally, the exclusion of individuals under legal protection (eg, guardianship) is required by French research regulations but may reduce generalizability to populations with severe cognitive impairment or psychiatric conditions, groups that may also experience an elevated risk of cardiovascular disease. Despite these limitations, this study addresses a critical gap in stroke prevention research in underserved populations and will provide valuable evidence on the effectiveness and scalability of community-based hypertension screening in resource-limited settings.

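### The confirmatory interrupted time series has no comparison series and no term for the pandemic years in its baseline, while the comparison meant to address temporal confounding is only a subanalysis

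*Protocol article*

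**What the plan says.** All references are to the protocol article.

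- **Confirmatory analysis.** Statistical Analysis, sample size paragraphs: "Both analyses will be reported, with ITS serving as the primary confirmatory analysis and the chi-square test as a sensitivity check".
- **Population and terms.** Statistical Analysis defines the primary contrast as "before and after the 2-year intervention period among residents of precarious neighborhoods within the CACL of French Guiana". It continues: "The ITS model will estimate the immediate change in level and the change in slope after the intervention", with autocorrelation and seasonality handled if diagnostics call for it. No comparison group appears in this model.
- **Series length.** Power is stated for one series: "On the basis of 60 monthly preintervention observations (5 years) and 24 monthly postintervention observations (2 years").
- **Place of the comparison areas.** Statistical Analysis, in the paragraph on secondary outcomes: "Subanalyses will compare trends in populations residing in intervention and nonintervention neighborhoods within the CACL", and also the intervention region with other parts of the territory. Secondary Objectives lists the same comparisons.
- **What they are relied on for.** Strengths and Limitations, after conceding that concurrent campaigns, access changes and secular trends could affect the outcome: "Although we will attempt to control for these through comparison with nonintervention regions in French Guiana, unmeasured confounding remains possible".
- **What the ITS is credited with.** Statistical Analysis says that the ITS itself deals with underlying trends and temporal confounders.
- **Calendar.** Results: "Recruitment for this study began in September 2023". Outcome Measures sets a 5-year baseline.

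**The concern.** The article names a remedy for temporal confounding and then leaves it out of the test that carries the conclusion. A segmented regression on one series adjusts for a smooth pre-trend and, if modelled, for season. It cannot tell the intervention apart from another change in admissions, coding or access that reaches the whole territory after September 2023. The chi-square sensitivity check makes the same uncontrolled before/after contrast, so it would not expose the problem.

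The baseline adds a second risk. The counterfactual is a line extrapolated from five years that include the pandemic. A temporary disturbance in those years tilts or shifts that line, and neither a seasonal term nor an autocorrelation term models it. At stake is whether a level or slope change can be attributed to the screening programme, and in the other direction whether a real benefit is understated.

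**Working it through.** **1. Rank of the comparator.** Let δ be the true effect and g a territory-wide proportional change in the post period that the pre-trend does not predict (log scale).

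- Single series: expected estimate = δ + g.
- Controlled series, if both areas share g: (δ + g) − g = δ.

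With δ = 0 and a 10% territory-wide change, the single-series ITS shows a 10% effect. This is a property of the design. It is not evidence that such a change occurred.

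**2. Baseline dates.** Start September 2023, minus 60 months: September 2018 to August 2023. March 2020 is month 19.

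**3. Effect of an assumed dip on the counterfactual.** Set the true level to 1 with no trend and no intervention effect. Reduce the chosen months by 10% or 20%, fit a straight line to months 1-60 by ordinary least squares, and average its extrapolation over months 61-84.

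| Dip | 10% | 20% |
|---|---|---|
| 6 months (19-24) | 1.003 | 1.005 |
| 12 months (19-30) | 0.997 | 0.994 |
| 22 months (19-40) | 0.968 | 0.937 |
| 24 months (19-42) | 0.960 | 0.920 |

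The last row can be checked by hand. Months 19-42 are centred on the baseline midpoint (30.5), so the fitted slope is 0 and the line sits at 1 − d × 24/60, which is 0.96 for d = 0.10 and 0.92 for d = 0.20. A longer dip (months 19-48) gives 0.929 and 0.858.

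**4. Same question in the planned model.** I fitted generalized least squares (GLS) with intercept, trend, level and slope change, and AR(1) errors. The inputs are the corners of the article's own ranges: ρ = 0.3 with coefficient of variation (CV) 15%, and ρ = 0.5 with CV 20%. For a 20% dip in months 19-42:

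- spurious average post-period effect: 7-8% of baseline (an apparent increase);
- spurious level change: 5.7-7.2%;
- slope term moved by at most 2.4% of baseline over 24 months;
- standard error of the average effect: 7.8% to 12.4% of baseline.

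The bias therefore falls mainly on the level term, and in these cases it is below or about one standard error.

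**5. Cost of an indicator.** Add a column equal to 1 in months 19-42 and compare √(L′(X′V⁻¹X)⁻¹L) with and without it, where L picks out the average effect. The bias from a constant dip becomes 0, and the standard error rises by 2-3%. Dropping those months instead raises it by 4-5%.

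**6. Cost of a control series.** The article gives about 350 strokes a year, of which 350 × 0.68 = 238 are in precarious patients. If 238 is the intervention series, everyone else totals at most 350 − 238 = 112 a year (112/12 ≈ 9 a month), including nonprecarious CACL residents. With Poisson variance the interval widens by √(1 + 238/112) = √3.125 ≈ 1.77, and by more for the smaller outside-CACL group.

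Even with a control of equal precision, power for a 30% average effect falls from 97% to 78% (ρ = 0.3, CV 15%) and from 68% to 40% (ρ = 0.5, CV 20%).

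**7. The article's own power figure.** It states more than 80% for a slope change corresponding to a 20-30% reduction. With level and slope terms I obtain 14-56% if that reduction is reached at month 24, and 40-98% if it is the 24-month mean. That is a separate matter; only the inputs are used here.

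**The case against.** **The comparison is planned and the risk disclosed.** This is true. The article plans comparisons both inside and outside the CACL, admits residual confounding, and promises only an attempt at control. A reader might infer from "is superior to standard health service delivery in reducing the incidence of stroke" that the primary objective demands a concurrent control. It does not: the same sentence sets the comparison against the preintervention period, so a before/after ITS answers the objective as written. A reader might also infer that the subanalyses exclude stroke because they sit in the secondary-outcomes paragraph; the text does not say so. What stands is the conflict between the reliance placed on these comparisons and their rank.

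**A pandemic term is SAP detail.** Covariates often are left to the SAP. But the article itself states the model terms and the baseline length, and the change is concrete and cheap, so it is worth raising. The documents never mention the pandemic. The overlap is calendar arithmetic, and the depth, length and direction of any disturbance are assumptions. A reader might infer that the baseline is biased; only a risk of bias is shown, and for a dip of a year or less it is negligible.

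**The bias would be conservative.** For a dip, yes: it hides benefit. A baseline excess of the same size would create apparent benefit.

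**The bias would swallow the expected effect.** A reader might dilute the planned 30% by partial reach and gradual rollout and conclude this. The documents give no diluted effect; they expect 20-30%. The point does not rest on such a comparison.

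**A controlled ITS costs too much precision to be the sole test.** This stands, on the counts in step 6. An interval only √2 times wider would need a control series of similar size, which those counts do not provide.

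**Conclusion.** The point holds in a limited form. The confirmatory ITS is uncontrolled, the comparison that the Limitations section leans on is ranked as a subanalysis, and the claim that a single series deals with temporal confounders is too strong. None of this depends on the pandemic.

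The baseline covers the pandemic years with no term for them. Under an assumed 10-20% fall lasting 22-24 months from March 2020, the counterfactual is 3-8% too low, mainly through the level term and against the intervention. Under a 6-12 month fall the shift is 1% or less.

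A reader might go further and conclude that the controlled ITS must replace the confirmatory test. The documents do not support that: on their counts the controlled contrast is much less precise, so replacement is a trade-off.

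The 1.8-fold figure assumes Poisson variance and that 238 of about 350 strokes a year fall in the intervention series. The article attributes the 350 to the whole territory in the Introduction and to the Cayenne hospital in the sample size section, so it should be checked against the extracted data.

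**What to change.** 1. **Baseline.** Add a pandemic-period indicator with fixed dates to the stroke ITS, and report a sensitivity fit that omits those months. Cost: the standard error of the average effect rises about 3% for a 24-month indicator, more for a longer one. An indicator removes only a constant shift, which is why the omission fit is also needed.

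2. **Comparator.** Name a controlled ITS for stroke as a key analysis reported beside the single-series ITS: intervention residents against areas of French Guiana outside the CACL, with the group-by-exposure term as the parameter of interest. Make any causal conclusion depend on the two agreeing. Use nonintervention zones inside the CACL as a spillover check only, because any CACL adult is eligible (Textbox 1) and recruitment used local radio (Participants).

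3. **Wording.** Limit the claim for the single-series ITS to adjustment for a smooth pre-trend and season.

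No new data collection is needed, since these comparisons are already planned. The downside is an imprecise controlled contrast (interval about 1.8 times wider or more on the counts above), so it needs its own precision statement and a prior definition of agreement that allows for the wide interval. Results scheduled the primary analysis for April-May 2026, before the article appeared; if it has been run, these changes must be labelled post hoc.

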#### Secondary Objectives

The secondary objectives are to evaluate the effectiveness of the intervention in reducing the incidence and mortality of other major cardiovascular and renal outcomes, including acute coronary syndrome (ACS), transient ischemic attack (TIA), peripheral artery disease (PAD), aneurysm, and ESRD; to assess participants’ adherence to referrals and satisfaction with the program; and to evaluate changes in screening coverage and antihypertensive treatment patterns. Comparisons will also be conducted between residents of targeted precarious neighborhoods and those living in nonintervention zones within and outside the intervention area.

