**Figure 1 figure1:**
[figure not shown]
Participant workflow during the study.

All interested participants receive a brief health education session covering hypertension awareness, associated dietary and lifestyle recommendations, and guidance on accessing health care entitlements. Participants may also be referred to other health care facilities or professionals in the event of health concerns other than hypertension. Subsequently, each participant undergoes standardized BP measurement using 3 readings spaced 1 to 2 minutes apart, including at least 1 reading from each arm, in accordance with European guidelines. If BP values suggest possible hypertension, participants are referred for medical evaluation either to a local physician or to the Permanence d’Accès aux Soins de Santé (PASS) based on their insurance status.

Suspected cases are provided with a formal referral document detailing the observed metrics to facilitate continuity of care within the health care system.

Participants identified with elevated BP are contacted by telephone at 3 months after inclusion (with an allowable variation of ±1 week) to assess diagnostic follow-through, treatment initiation, and compliance with medical recommendations. During this follow-up, mediators reinforce the importance of ongoing care if lapses are identified.

In parallel, after the mediators have provided oral information about the study, they verify the inclusion (age ≥18 years, residence in the CACL, and absence of legal protection) and exclusion criteria and obtain the participant’s nonopposition to participation. For these participants, an additional structured questionnaire is administered to collect sociodemographic and anthropometric data, cardiovascular history, prior diagnoses, medication adherence, barriers to health care access, and a satisfaction survey.

Withdrawal from the study is permitted at any time without justification and does not affect access to usual medical care. Investigators may also discontinue participation if continued participation is deemed not to be in the participant’s best interest. Reasons for withdrawal or loss to follow-up will be recorded when available.

Figure 2 outlines the stepwise procedure for participant inclusion, assessment, and subsequent actions based on BP results and health insurance status, including interventions, referrals, and follow-up steps.

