### Intervention or Treatment

The intervention will consist of a comprehensive, community-delivered hypertension screening and education program. It will be implemented by 12 trained health mediators organized into 3 teams of 3 to 4 mediators each. The protocol stipulates that each mediator can screen approximately 10 people per day, representing a target of 2000 adults per month. These mediators, certified through a university-level diploma in health mediation or with equivalent field experience, will engage directly with residents in all precarious neighborhoods within the CACL. Each neighborhood will receive at least 1 intervention visit during the 24-month intervention period. The number of visits per neighborhood will be determined based on population size and accessibility. The goal is comprehensive coverage of an estimated population of 50,000 adults in the target neighborhoods.

To maximize reach, each visit will last 1 to 2 days, with mediators establishing fixed screening posts and conducting door-to-door outreach. The quantification of coverage will not be based solely on the number of individuals screened but on the number of neighborhoods fully investigated by the mediators. The intervention will be considered complete for a neighborhood when the minimum number of planned visits has been conducted, when mediators have systematically covered all streets or sectors through door-to-door approaches, or when repeated visits yield diminishing returns.

Given population mobility and the informal nature of precarious settlements, we acknowledge that precise denominator estimation is challenging. Mediators will set up mobile stations or conduct home visits to measure BP triadically according to European guidelines, provide personalized health education focused on hypertension and lifestyle modification, assess health insurance coverage, and guide participants with elevated BP to appropriate health care professionals or social services (eg, general practitioners or the PASS unit). Follow-up will include a structured telephone call 3 months later to assess completion of the medical referral process.

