### Outcome Measures

The primary outcome will be the change in the incidence of stroke comparing the 5-year preintervention period with the 2-year period following the start of the intervention, as recorded in the Programme de Médicalisation des Systèmes d’Information (PMSI) database. Secondary outcomes will include changes in incidence of ACS [28], TIA [29], PAD [30], aneurysm, and ESRD [31] (*insuffisance rénale terminale* [IRT]), as well as all-cause cardiovascular mortality within 1, 2, and 3 years after the intervention. ACS refers to a spectrum of urgent cardiac conditions caused by a sudden reduction in blood flow to the heart muscle due to a partial or complete blockage of the coronary arteries. This group of conditions includes unstable angina and non–ST-elevation myocardial infarction (NSTEMI), both of which require prompt diagnosis and individualized treatment strategies to prevent further cardiac damage and improve patient outcomes.

ESRD represents the final and most advanced stage of chronic kidney disease, defined by a severely reduced GFR of less than 15 mL/min/1.73 m^2^. At this stage, patients require kidney replacement therapy, which includes either long-term dialysis or kidney transplantation. ESRD is a chronic condition that typically arises in the context of long-standing comorbidities, notably hypertension.

PAD is a circulatory condition characterized by the narrowing or blockage of peripheral arteries, most commonly in the lower limbs, due to the buildup of atherosclerotic plaques. This reduced blood flow can lead to symptoms such as leg pain during walking (claudication), numbness, or even tissue damage in severe cases. Importantly, PAD is not confined to the extremities; it reflects a systemic atherosclerotic process that affects multiple vascular beds. As such, PAD serves as a clinical marker for widespread vascular dysfunction and is strongly associated with an elevated risk of major cardiovascular events, including myocardial infarction and stroke.

Additional secondary end points will assess participants’ adherence to medical referrals, satisfaction with the program, the number of BP screenings completed, the number of new or rediagnosed hypertensive cases, and changes in antihypertensive prescription patterns using health insurance data. Outcome assessments will be based solely on administrative records and structured questionnaires, minimizing subjectivity and measurement variability.

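### Reimbursed prescription volume is read as a population-level treatment effect, but the intervention also acts on insurance coverage and so can change who appears in that source at the tested break

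*Protocol article*

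**What the plan says.** All references are to the protocol article.

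- **Objective** (Secondary Objectives): "to evaluate changes in screening coverage and antihypertensive treatment patterns".
- **Endpoint and source** (Outcome Measures): "changes in antihypertensive prescription patterns using health insurance data".
- **Metric and method** (Statistical Analysis): "Trends in antihypertensive prescription volumes, obtained from health insurance reimbursement data, will also be evaluated over the preintervention and postintervention periods using ITS models". The stated purpose is "to assess the effect of the intervention at the population level".
- **What the programme does about coverage.** The education session given to all interested participants includes "guidance on accessing health care entitlements" (Study Design and Setting). Mediators also "assess health insurance coverage, and guide participants with elevated BP to appropriate health care professionals or social services" (Intervention or Treatment).
- **Referral route** (Study Design and Setting): people with suspected hypertension are sent "either to a local physician or to the Permanence d’Accès aux Soins de Santé (PASS) based on their insurance status".
- **Uncovered people** (Statistical Analysis): comparisons are to be stratified by coverage markers, the last being "or absence of coverage) when available in the source databases". People without coverage are therefore expected in the population.

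**The concern.** A reimbursement database records people through their coverage. A raw count of reimbursed prescriptions is therefore the product of two things: how many people are treated, and how many of those are visible to the insurer. An ITS on that count can be read as a treatment effect only if visibility does not move at the break. Here the intervention works on both.

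Two distortions are possible, in opposite directions:

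- Someone already treated without coverage who gains it after the programme starts adds volume with no change in treatment.
- Someone who starts treatment outside reimbursement adds treatment with no change in volume.

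This series is the only planned measure of treatment with a long pre-intervention run at population level. It is the natural evidence for the step between screening and stroke. A coverage artefact could lend that step false support, or hide a real gain.

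**Working it through.** The article gives no effect size, power or insured share for this endpoint, so there is no stated figure to reproduce. The calculation below shows only how large the artefact could be.

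**Inputs from the article**

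- People reached: 23,289 (Results).
- Estimated adults in the target neighborhoods: 50,000 (Intervention or Treatment).
- Reach r = 23,289 / 50,000 = 0.466.

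**Inputs assumed, not in the article**

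- u, the share of treated people who are uninsured before the programme: 5% to 40%.
- g, the share of reached, uninsured, already treated people who gain coverage: 10% to 100%.
- Uninsured treated people are reached in the same proportion as everyone else, and volume per treated person is equal and constant.

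**Step 1: spurious rise with treatment unchanged.** If T people are treated, T(1 − u) are visible beforehand and T·r·g·u become visible. The relative rise is r·g·u / (1 − u):

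| u | g = 10% | g = 25% | g = 50% | g = 100% |
|---|---|---|---|---|
| 5% | 0.2% | 0.6% | 1.2% | 2.5% |
| 10% | 0.5% | 1.3% | 2.6% | 5.2% |
| 20% | 1.2% | 2.9% | 5.8% | 11.6% |
| 30% | 2.0% | 5.0% | 10.0% | 20.0% |
| 40% | 3.1% | 7.8% | 15.5% | 31.1% |

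For example, u = 20% and g = 25% give 0.466 × 0.25 × 0.20/0.80 = 2.9%. With u = 30% and g = 50%, 0.466 × 0.50 × 0.30/0.70 = 10.0%. These apply to a series restricted to the target population once the full reach is attained. Earlier months, or a wider catchment, would show less.

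**Step 2: true rise with coverage unchanged.** Let treated people rise by a fraction D, with a share q of new starts not reimbursed. The observed rise is D(1 − q) / (1 − u). With D = 20% and u = 20%:

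- q = 0: 0.20 × 1.0 / 0.80 = 25.0%
- q = 50%: 0.20 × 0.5 / 0.80 = 12.5%
- q = 100%: 0

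The series is right only when q equals u, so the bias can go either way.

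**Step 3: do the planned safeguards remove it?**

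- *ITS* accounts for the trend before the break. A visibility change that begins with the programme is not part of that trend.
- *Comparison areas* do not receive the programme's entitlement guidance, so the contrast keeps the artefact.
- *Stratifying by coverage* conditions on something the programme can alter, and applies only where the databases hold the marker. People without coverage would not generate reimbursement records.
- *Strengths and Limitations* names changed access to care only as a confounder acting independently of the intervention, alongside coding and diagnostic practice. A change in capture caused by the intervention is not mentioned.

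**The case against.** The strongest reply has four parts.

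1. **No one is shown to have gained coverage.** The article describes guidance, assessment and referral to social services, and gives no count of people newly covered. This stands: the programme *can* change coverage, and no more can be said. A reader might infer large shifts, such as an insured share rising from 80% to 90% (a 12.5% artefact, 90/80) or from 70% to 85% (21%, 85/70). With proportional reach these do not fit. The first needs 5,000 newly covered adults against about 4,660 uninsured adults reached (0.466 × 10,000). The second needs 7,500 against about 6,990 (0.466 × 15,000). Even 80% to 85% needs 2,500 of 4,660, or 54%. Those ratios also assume uninsured adults are already treated as often as insured ones. An untreated person who gains coverage and then starts treatment is a real effect.

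2. **Treatment starts among uninsured people are recorded elsewhere.** This also stands. The 3-month call asks about treatment initiation and questionnaire treatment uptake gets paired tests, neither depending on reimbursement. But both are self-reported, the call covers only people with elevated readings, and neither is described with a five-year pre-period or comparison area. They supplement the series and cannot replace it.

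3. **Treatment begun through the PASS may be reimbursed.** The article does not say. That it escapes the data is an assumption, and q in step 2 is unknown.

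4. **Denominators and cohort definitions belong in the analysis plan.** True in general. The point here is not missing detail: the article fixes metric, source, method and inference, and that combination is open to bias.

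**Conclusion.** The concern holds in a limited form. Reimbursed volume under ITS cannot by itself separate a change in treatment from a change in coverage, because the intervention may alter both from the same date. The size and even the sign are unknown. With treatment unchanged, the spurious rise runs from about 0.2% to 31% over the assumed inputs, and about 3% to 10% at mid-range inputs. These figures rest on proportional reach of 46.6% and on assumed values of u and g.

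Two stronger readings are not supported: that the programme demonstrably moves uninsured people into coverage, and that their treatment goes unseen by the study. The point touches one secondary endpoint and its population-level interpretation. The stroke outcome, taken from hospital discharge data, is unaffected.

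**What to change.** In Outcome Measures and Statistical Analysis, keep the volume series and add:

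- (a) the monthly number of covered adults, as its own ITS series;
- (b) the monthly proportion of covered adults with at least one antihypertensive dispensing;
- (c) a sensitivity series in adults already covered before September 2023, adjusted for age, with newly covered adults shown separately. State how membership is defined across the pre-intervention years.

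Attribute a change in volume to treatment only if (b) and (c) agree with it. State whether treatment begun through the PASS reaches the reimbursement data, and set the result beside self-reported treatment initiation at 3 months, by insurance status. If the reimbursement series have already been examined, label the additions accordingly.

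**Cost.** Some extra extraction and analysis of administrative data, and no fieldwork. Series (b) can be diluted by newly covered adults who are untreated. Series (c) leaves out the newly covered, a group the programme wants to reach, which is why it should not become the main series. A real effect confined to that group could therefore go uncredited, so the series must be read together.
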